### Ethical issues

The present study complies with the stipulations in the “Declaration of Helsinki” for research involving human beings and with the Brazilian Ministry of Health’s National Health Council Resolution 466/2012 [54]. The internal review board of the Medical Sciences Centre (CCM), Federal University of Paraíba (UFPB) approved the study protocol under reference CAAE 71621717.9.0000.8069, www.plataformabrasil.saude.gov.br.

All of the participants will be informed as to the objectives of the study and will only be included in the study should they agree to participate and sign an informed consent form.

## Discussion

Although laparoscopic cystectomy is the gold standard for the treatment of endometrioma, there are some risks associated with the procedure that may damage ovarian function, even when performed by experienced surgeons [17]. There is considerable controversy in the literature regarding which hemostatic technique causes less damage to the ovarian parenchyma following the stripping of the endometrioma capsule.

To the best of our knowledge, this is the first study to compare three different hemostasis techniques in a single clinical trial, including a detailed assessment of bipolar use. The number of points to be coagulated will be analyzed descriptively, since randomization would risk coagulating more points than required or preventing coagulation when necessary. We believe that the use of bipolar energy may interfere with ovarian function and its judicious use may be associated with less damage; therefore, this variable should be described in detail.

Given the data presently available in the literature, we would like to add to current knowledge by answering the following questions with this RCT:Is bipolar energy really responsible for ovarian damage? andIs surgical treatment responsible for ovarian damage irrespective of the hemostatic technique used?

Our findings may help surgeons choose the hemostatic method that would cause less damage to ovarian function or, if there are no significant differences between the methods evaluated in this study, surgeons will then be able to choose the most convenient method according to its availability in that particular facility.

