**Discussion:**

Bearing in mind the need for more randomized clinical trials to clarify this issue, we hope to contribute with data that will determine whether there is any difference between hemostatic methods despite the rational use of bipolar energy or whether the procedure itself explains the ovarian damage irrespective of the hemostatic technique used.

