### Sample size

Sample size was calculated using resources available at the Laboratory of Epidemiology and Statistics (LEE) website of the Dante Pazzanese Institute (http://www.lee.dante.br/pesquisa/amostragem/qua_2_medias.html). The calculation was based on data provided by Sönmezer et al. [48]. In that article, Sönmezer et al. detected a significant difference in the serum levels of AMH in the first month after surgery, with a measurement of 2.72 ± 1.49 for the patients who received the hemostatic matrix versus 1.64 ± 0.93 for the patients who received bipolar coagulation. Here, we assume that the standard deviation in the AMH measurement of 1.49 in the first month was significant, since that was the number that generated the largest sample size when compared with other values from that article. The difference to be detected is 1.08, which corresponds to the mean difference in AMH in the first month between the patients who receive hemostatic matrix and those who receive bipolar coagulation. On those grounds, and for a statistical power of 80% (*p* = 0.05), each group would have to have 23 participants. Considering possible losses, the sample will be increased by 20% to 28 participants per group, making a total of 84 women. It should be noted that the present sample maybe not detect a powerful difference in treatment arms, but relevant contributions are expected.

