#### Data processing and analysis

The data will be double-entered by two different data entry operators, using the Epi Info software program, version 7.2. The two databases will be compared using the Validate function of the Epi Info software program. Statistical analysis will be conducted using the Microsoft Excel software and the SPSS statistical software package for Windows, version 19.0.0. The data entry operators and the statistician will be blinded in that they will receive the data marked simply as A, B, or C and will be unaware of which procedure corresponds to which letter. A significance level of 5% will be determined for all the statistical tests.

To analyze the numerical variables AMH and AFC, the Kolmogorov–Smirnov test of normality will be used to determine the type of analysis to be performed. If distribution is normal, two-way analysis of variance (ANOVA) will be used, with the group representing an independent factor (bipolar energy × suture × hemostatic matrix). Another factor to be analyzed will be paired time points (before surgery × 1 month × 3 months × 6 months). If distribution is not normal, non-parametric tests will be used to analyze the variables.

The Kruskal–Wallis test will be used to compare variables between the three groups at each time point, with Tukey’s multiple comparison test being used when comparisons are statistically significant. The Friedman test will be used to perform intra-group comparisons at the four evaluation moments, with Tukey’s multiple comparison test being used when they are significant.

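### The Discussion lets a non-significant result justify choosing the hemostatic method by convenience, with no margin or confidence-interval criterion behind it

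*Protocol article*

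**What the plan says.** The last paragraph of the article's Discussion sets out two uses of the results. The findings may help surgeons pick the less damaging method, or, "if there are no significant differences between the methods evaluated in this study, surgeons will then be able to choose the most convenient method", guided by what the facility has available.

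The abstract's discussion has a related aim: to learn whether the methods differ or "whether the procedure itself explains the ovarian damage irrespective of the hemostatic technique used".

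The Sample size section rests on one comparison at one time point. It says: "The difference to be detected is 1.08, which corresponds to the mean difference in AMH in the first month", between matrix and bipolar coagulation, and adopts the larger source SD, 1.49. It then concedes that "the present sample maybe not detect a powerful difference in treatment arms".

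The section on data processing and analysis plans two-way ANOVA or, if normality fails, Kruskal–Wallis and Friedman tests with Tukey comparisons after a significant result. It adds: "A significance level of 5% will be determined for all the statistical tests". All of these test for a difference. The article gives no equivalence or non-inferiority margin and no rule based on an interval.

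**The concern.** A superiority test that fails to reject leaves two explanations open: the methods are alike, or the data are too few to separate them. The Discussion sentence treats the first as established, and the caveat in the Sample size section is not carried over to it.

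The consequence is practical. The Background says most investigators hold bipolar coagulation responsible for a decrease in ovarian function compared with suture or hemostatic agents. An inconclusive trial, read as the Discussion proposes, would put all three methods on an equal footing for ovarian reserve when the data might still be compatible with a difference as large as the one the trial was designed to find.

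**Working it through.** **Inputs (Sample size section).** Difference 1.08; SD 1.49; source values "with a measurement of 2.72 ± 1.49 for the patients who received the hemostatic matrix versus 1.64 ± 0.93"; power 80%; significance level 0.05, sidedness not stated; 23 per arm needed, 28 enrolled after adding 20%, 84 in total. The figures below assume normally distributed AMH with a common SD and ignore any gain from baseline or repeated measures.

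**1. The plan's own figure.** n per arm = 2(z_α + z_β)² SD²/difference².
- One-sided 5%: 2 × (1.645 + 0.842)² × 1.49²/1.08² = 23.5, that is 24, close to the stated 23.
- Two-sided 5%: 2 × (1.960 + 0.842)² × 1.49²/1.08² = 29.9, that is 30.
- Two-sided with both source SDs: (1.960 + 0.842)² × (1.49² + 0.93²)/1.08² gives 21, but the text says 1.49 was used.
- 23 × 1.2 = 27.6, so 28; 28 × 3 = 84.

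So 23 per arm at SD 1.49 corresponds to about 80% power only for a one-sided test.

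**2. Precision of one pairwise difference.** SE = 1.49 × √(2/n): 0.439 at 23 and 0.398 at 28. Half-width of the 95% CI = critical value × SE.

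| | 23 per arm | 28 per arm |
|---|---|---|
| Unadjusted t | 0.89 | 0.80 |
| Tukey, three groups | 1.05 | 0.95 |

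All four are below 1.08. An observed difference near 0 would therefore exclude 1.08. At 23 per arm, a non-significant observed difference between 1.08 − 0.89 = 0.19 and 0.89 would not (0.03 to 1.05 with Tukey).

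**3. Chance of missing a real difference (two-sided 5%).** The normal approximation at 23 per arm gives 1.08/0.439 − 1.960 = 0.498, so power 69%. The noncentral t gives 67%, so a miss rate of 33%.

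| True difference | 23 per arm | 28 per arm |
|---|---|---|
| 1.08, unadjusted | 33% | 24% |
| 1.08, Tukey, single pair | 47% | 37% |
| 0.54, unadjusted | 77% | 73% |

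**4. What a non-significant interval still allows when the true difference is 0.** First hold the half-width fixed at 1.96 × SE = 0.861 (23 per arm). The interval then reaches ±1.08 when the observed difference exceeds 1.08 − 0.861 = 0.219 in size. P(0.219 < |D| < 0.861) = 0.568 and P(non-significant) = 0.950, so the share is 0.568/0.950 = 60%. At 28 per arm it is 0.402/0.950 = 42%. Simulation with the SD estimated from the data gives 64% and 45%. These count 1.08 in either direction; by symmetry, one named direction accounts for about half (32% and 23%).

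For all three pairs together, with the methods truly equal and no pair significant, all three Tukey intervals exclude 1.08 in about 2% of trials at 23 per arm and 8% at 28.

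**5. Sensitivity to the SD.** Pooling the two source SDs gives √((1.49² + 0.93²)/2) = 1.24. The half-widths become 0.74 and 0.67. The unadjusted miss rates at 1.08 become 18% (23 per arm) and 11% (28). The fixed-half-width shares in step 4 fall from 60% and 42% to 29% and 15%.

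**The case against.** The strongest reply is that this is a Discussion sentence about possible use, not an analysis rule. It begins by saying the findings may help, and the analysis section contains no procedure for declaring equivalence. The Sample size section also discloses that a difference may go undetected. SD 1.49 is the larger of two values, and with the pooled SD the miss rates are modest.

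Much of this is fair, and it limits the point. But the hedge governs the first half of the sentence; the step from no significant difference to free choice is unhedged and is one of two outcomes the authors plan for. Disclosing limited power in one section does not repair an inference in another that ignores it. The pooled SD lowers the figures without making non-significance evidence of similarity.

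Three stronger readings are tempting and are not supported:
- *That the trial cannot exclude 1.08.* Every half-width above is below 1.08, so a result close to 0 can exclude it, though only narrowly with Tukey intervals at 23 per arm.
- *That the plan treats non-significance as proof.* The article does not say so; it draws a practical conclusion.
- *That the abstract asserts that surgery itself explains the damage.* It poses a question. Whether reserve falls after surgery within each arm is addressed by the planned comparison of the four time points. Only the between-arm part, irrespective of technique, depends on a null comparison.

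**Conclusion.** The point holds as a fault of interpretation. The Discussion moves from no significant difference to choice by convenience, and nothing in the design or planned analysis supports that step. On the plan's SD and two-sided tests, a true difference of 1.08 is missed in roughly a quarter to a third of trials (37% to 47% with Tukey adjustment), and one of 0.54 in about three quarters. When the methods are truly equal, a non-significant pair still leaves 1.08 open in one direction or the other in about 64% of cases at 23 per arm and 45% at 28. The pooled SD gives smaller figures and the same conclusion.

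These sizes rest on normal AMH, a common SD and a month-1 comparison without baseline adjustment; a more efficient analysis would narrow the intervals. Allocation, measurements and tests are unaffected, and the fault can be cured before or at reporting.

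**What to change.** Replace the Discussion sentence with wording to this effect: a non-significant comparison will be reported as inconclusive and not as grounds for choosing by convenience; all three pairwise AMH differences will be given with Tukey-adjusted 95% CIs, stating which differences they exclude; interchangeability will be claimed only if the intervals lie within a clinically justified margin fixed before the results are known. Apply the same caution to the between-arm part of the aim in the abstract.

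The documents give no basis for a margin, so the sponsor would have to justify one. Trial status reports 32 of 84 randomized in April 2019, so at that date it could still be set ahead of the results. If no margin can be justified, dropping the convenience inference and reporting the intervals is enough.

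The cost in text is one paragraph. The real cost is that a null result will probably be called inconclusive. As an illustration only, take a margin of ±1.08, SD 1.49, a true difference of 0 and 80% power. Two one-sided tests on one pair, unadjusted for multiplicity, need 2 × (1.645 + 1.282)² × 1.49²/1.08², that is 33 per arm with a 90% CI, or 40 with a 95% CI. Half that margin, 0.54, needs 131 or 160. The plan has 23 evaluable and 28 enrolled.

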### Trial status

Randomization began on 15 March 2018, with 32 patients having been randomized to date (24 April 2019).

## Data Availability

The datasets used and/or analyzed during the current study are available from the corresponding author upon reasonable request.

## Abbreviations

AFC: Antral follicle count
AMH: Anti-Müllerian Hormone
ANOVA: Analysis of variance
ASRM: American Society for Reproductive Medicine
CAAE: Certificate of Presentation for Ethical Assessment
CCM: Medical Sciences Centre
ELISA: Enzyme-linked immunosorbent assay
FSH: Follicle-stimulating hormone
HULW: Lauro Wanderley University Hospital
LEE: Laboratory of Epidemiology and Statistics
RCT: Randomized clinical trial
UFPB: Federal University of Paraíba
USA: United States of America
